### Sample size

For feasibility and pilot studies, sample sizes between 24 and 50 have been recommended to estimate a chosen parameter.^31 32^ Using a 1:1 treatment to control ratio, a total sample size of 60 would be sufficient to estimate the SD of the outcome of at least 28 treated participants per group, with 7% attrition. We aim to estimate the screening success (assumed as 70%; 95% CI 60% to 80%) from approximately 105 potentially eligible participants.

Of the 60 participants, we will enrol at least 16 with small FTMHs (<250 µm minimum linear diameter), 16 medium (250–400 µm) and 16 large (>400 µm). We feel it is appropriate to recruit holes of varying size. This will support generalisability and provide the evidence needed to inform a future study design.

### Recruitment

With the anticipated recruitment rate of 0.5 participants/site/month, this gives an expected final patient recruited date of 23 months after trial start, in February 2026. A follow-up will finish 6 months following the recruitment of the final participant.

### Assignment of interventions

Participants will be randomised at the time of screening once the investigator has confirmed eligibility, and a decision has been made regarding combined surgery.

Participants will undergo randomisation by the process of minimisation, prior to surgery in a ratio of 1:1. They will be stratified based on planned operation (combined procedure or FTMH surgery alone) and FTMH size (small, medium and large). Phacoemulsification and IOL implant can be performed prior to vitrectomy in a ‘combined procedure’ if deemed appropriate, but the decision to undertake phacoemulsification should be made prior to randomisation.

A web-based bespoke randomisation system has been created in collaboration with the trial statisticians and the chief investigator (CI) and maintained by the KCTU for the duration of the project. It will be hosted on a dedicated server within King’s College London.

### Allocation concealment mechanism

Site-level investigators will have individual password protected access to the randomisation system. Through this, you will be informed of the study arm allocation from the central randomisation service once patients have enrolled onto the study and are determined to be eligible.

### Who will be blinded?

BCVA and central optical coherence tomography (OCT) assessors will be masked to study treatment allocation. Due to the presence of gas within the eye, it is not possible to mask participants, and while still in the eye, it is also not possible to mask BCVA assessors. Hence, the BCVA assessments on day 1, day 7 and month 1 will be performed by an unmasked assessor, as the gas will probably be present at these visits. The assessment of OCT images at a site level is not masked, but a masked grader will assess OCT images sent to an independent reading centre, to determine the OCT-based efficacy outcome measure (anatomic closure).

### Procedure for unblinding

Not applicable.

### Plans for assessment and collection of outcomes

The main feasibility outcomes will be collected through data available on the central electronic data capture (EDC) system. Sites will use corresponding paper case report forms (CRFs) to complete and upload the data onto the EDC from where it will be analysed by trial statisticians. Electronic versions of the paper CRFs will be made available to each site. Baseline demographic, ophthalmic and medical history will be recorded, including the duration of FTMH-related symptoms.

For the efficacy outcomes, full refracted best-corrected ETDRS visual acuity assessment will be performed by a qualified masked examiner. It will be performed at screening and at the postoperative visits at months 3 and 6, starting with testing at a distance of 4 m. Unmasked ETDRS visual acuity will be measured at all other visits.

OCTs will be performed at each study visit except for the day of surgery (it may not be possible to perform the postoperative OCT imaging in the control group until the gas tamponade absorbs). Heidelberg Spectralis spectral domain OCT will be used to capture a macular raster scan with a minimum size of 10^0^×20^0^, consisting of 50 sections with 60 µm spacing, centred on the fovea. An additional radial scan will be captured, consisting of 6 lines centred on the fovea.

The minimum linear diameter and base FTMH diameter will be measured with the calliper tool on the Heidelberg Eye Explorer platform, in the scan with the greatest hole width. Images will be read by the attending clinical investigator to measure the hole minimum linear and basal diameter, subsequently determine if the hole has closed, and describe the pattern of closure.^33^

Determination of development or progression of lens opacity will be measured by the mean change in LOCS2 grading.^34^

Quality of life measures will be assessed by the NEI VFQ-25 visual function questionnaire, measured at the baseline and month 6 time points. The macular treatment satisfaction questionnaire (MacTSQ; available from healthpsychologyresearch.com) will be used to assess the acceptability of treatment and will be measured at each postoperative visit.^35^

### Plans to promote participant retention

The design of the study has been chosen to replicate the normal care pathway for patients undergoing treatment for FTMH. This will limit the amount of additional burden participants will experience as part of the study and should benefit retention. Participants who chose to withdraw will be asked to complete an optional end of study visit that has all the assessments included in the month 6 visit.

### Data management

Sites will be provided with paper CRFs to complete during study visits. These correspond to a bespoke online EDC system that has been developed for the study to collect and store the relevant data. The EDC has been developed by the CI and analysts in collaboration with the KCTU. It is based on the MACRO system and is compliant with all relevant regulations. The EDC will be password-protected and reside on a secure server hosted by King’s College London.

#### Data quality processes

The CI team will undertake appropriate reviews of the entered data, in consultation with the project analyst, for the purpose of data cleaning and will request amendments as required. No data will be amended independently of the study site responsible for entering the data.

### Statistical methods

#### Statistical methods for primary and secondary outcomes

The proportion of patients who are successfully recruited after screening will be reported with 95% CIs computed by the exact binomial method, as will all outcomes assessing feasibility except for recruitment rate, which will be reported per site per month. In addition to summary statistics of the secondary outcomes (similarly to the primary and baseline outcomes), all harms and withdrawals will be reported with 95% CIs.

An exploratory efficacy analysis will be based on intent-to-treat and include all randomised participants. A secondary analysis will be per protocol comparing those who had gasless vs standard surgery, irrespective of allocation, to investigate the effect of cross-over. The safety population will include all participants who underwent randomisation.

The proportion of participants with primary surgical anatomical closure and mean BCVA (change from baseline, and area under the curve (AUC)) will be compared between groups at 6 months (Fisher’s exact test and Mann-Whitney, respectively). For the AUC analysis, VA will often be below 1 ETDRS letter when gas is in the eye, so ETDRS acuity will be converted to logarithm of the minimum angle of resolution (logMAR) with assignment of logMAR values to count fingers or worse^36^:

Count fingers at 2 ft: logMAR+1.85.

Hand motions at 2 ft: logMAR+2.3.

Visual acuity of ‘light perception’ or ‘no light perception’ will not be converted and will be reported separately.

Adherence to posturing and treatment acceptability will be described.

The MacTSQ has been validated for use in macular diseases requiring drug administration and consists of two subscales: information provision/convenience and treatment satisfaction.^35^ The individual scores from each subscale as well as the composite score will be analysed based on change from the first time point (paired sample t-test) and between groups (analysis of variance model).

Quantifiable findings from the MacTSQ will be analysed using descriptive statistics. Open-ended responses will be analysed for descriptive and analytic accounts using thematic analysis and a constant comparison approach. Analysis will pay particular attention to key factors that impact on patient experiences both positively and negatively and will integrate quantifiable data from the MacTSQ in the analysis to investigate patterns of experience within the participant population.

A detailed Statistical Analysis Plan has been prepared prior to the start of recruitment.

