### Intervention

Eligible patients will be randomised at baseline to one of two treatment arms in a 1:1 ratio through the King’s Clinical Trials Unit (KCTU)’s randomisation platform to either:

PPV, ILM flap and viscoelastic coating without gas tamponade.PPV, ILM peel and 16% C2F6 gas tamponade with 5 days face down posturing.

FTMH surgery will be performed by a trial approved consultant vitreoretinal surgeon, most usually the site’s principal investigator (PI), under local anaesthesia, with or without sedation, or general anaesthesia. Surgery comprises core 23G, 25G or 27G PPV, induction of posterior vitreous detachment if required, and peripheral vitrectomy.

The surgeon’s preferred licensed macular vital stain will be used to stain the ILM.

The gasless surgical technique is based on Stopa *et al*’s description, wherein a hinged ILM flap is created under heavy liquid, then folded over the FTMH. The use of heavy liquid for flap creation is optional and based on surgeon experience and preference. A surgical video is provided in Stopa’s report.^24^

The only deviation from Stopa’s technique is that, where possible, a superior flap should be created, so that gravity helps hold it over the macula. Variations may be necessary as sometimes ILM peeling can be difficult to guide precisely (eg, the discarded flap may be used as the free cover if the folded flap does not position as desired).

A layer of Healon Pro viscoelastic will be applied to the macular area to help hold the flap in place, under heavy liquid. If necessary to retain the flap in position, the flap may be tucked into the hole. Heavy liquid will then be removed. If Healon Pro is not readily available at a study site, then an equivalent Conformité Européenne (CE)-marked OVD licensed for use in the eye may be used, subject to approval from the sponsor.

The aim is to seal the hole with ILM/viscoelastic, as our mechanistic hypothesis is that fluid flow through the hole maintains patency. However, tamponade will be used if it is not technically possible to occlude the hole using a combination of ILM and OVD.

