#### Feasibility outcomes

Screen failure (proportion of those screened).Recruitment rate (participants per site per month).Participant retention (proportion reaching month 6 milestone).Cross-over (proportion converting to standard vitrectomy with gas, due to inability to seal the FTMH, or detection of peripheral retinal breaks).

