#### Safety outcomes

Adverse events (AEs).Intraoperative and postoperative complications.Development or progression of lens opacity within 6 months of vitrectomy (proportion undergoing or listed for cataract surgery and mean change in Lens Opacities Classification System 2 (LOCS2) grading).

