**Figure 1 F1:**
[figure not shown]
Study flow chart. C_2_F_6_, hexafluoroethane; FTMH, full-thickness macular hole; MacTSQ, Macular Disease Treatment Satisfaction Questionnaire; n, number; NEI VFQ-25, National Eye Institute 25-Item Visual Function Questionnaire.

Screening will occur once the participant has given their written informed consent, and surgery defines the baseline visit. Participants will be randomised at the time of screening once the investigator has confirmed eligibility and a decision has been made regarding combined surgery.

Participants will be seen for follow-up according to a typical standard of care, with appointments at day 1, week 1, month 1, month 3 and month 6. A summary of the trial procedures at each appointment is included in table 1.

**Table 1 T1:** Schedule of study assessments, summary of visit activities

Activity	Screening	Baseline	D1	W1	M1	M3	M6
Visit window (±days)	Day −42 to 0	–	0	±3	±7	±7	±7
Consent	X						
Medical and ophthalmic history	X						
Randomisation	X						
Vitrectomy		X					
Full refracted ETDRS BCVA	X					X	X
Clinic ETDRS VA*			X	X	X		
Service user questionnaire (posturing compliance)			X	X			
Macular Disease Treatment Satisfaction Questionnaire			X	X	X	X	X
Visual Function Questionnaire 25-Item	X						X
Slit-lamp examination and IOP	X		X	X	X	X	X
Lens grading	X		X	X	X	X	X
OCT (if possible)†	X		X†	X†	X	X	X
Adverse events (safety)	X	X	X	X	X	X	X
Concomitant medications	X	X	X	X	X	X	X

* Clinic ETDRS VA should be undertaken in the study eye only using an ETDRS chart with correction of any refractive error, with and without. pinhole. This should be undertaken by unmasked assessors at day 1, week 1 and month 1 in both arms. Thereafter from month 3, only suitably trained and delegated masked assessors should undertake Full refracted ETDRS BCVA.

† OCT at the ‘day 1’ and ‘week 1’ visits may not be possible in those receiving gas tamponade and may be omitted at these two visits for participants in the control arm. OCT must be performed in the study eye for all participants at all other visits, and at the day 1 and week 1 visits for those in the novel surgery arm.

BCVA, best-corrected VA; ETDRS, Early Treatment Diabetic Retinopathy Study; IOP, intraocular pressure; OCT, optical coherence tomography; VA, visual acuity; VFQ-25, National Eye Institute 25-Item Visual Function Questionnaire.

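### The safety population is everyone randomised, with no requirement that surgery took place and no stated grouping for converted eyes, so surgical harm rates can be diluted and the gas versus gasless contrast blurred

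*Protocol article*

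**What the plan says.** The protocol article, under statistical methods for primary and secondary outcomes, fixes the safety set in one sentence: "The safety population will include all participants who underwent randomisation". It names neither surgery as a condition nor the grouping to be used.

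On timing, the participant timeline section says "Participants will be randomised at the time of screening once the investigator has confirmed eligibility" and adds that "surgery defines the baseline visit". The section on assignment of interventions agrees, and Table 1 marks randomisation in the screening column, whose window is Day −42 to 0. The Intervention section differs: "Eligible patients will be randomised at baseline to one of two treatment arms in a 1:1 ratio".

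On what can be counted, the safety outcomes include "Intraoperative and postoperative complications". The Harms section records adverse events from consent onwards.

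On treatment actually received, the Intervention section says "tamponade will be used if it is not technically possible to occlude the hole using a combination of ILM and OVD". The feasibility outcomes define cross-over as the "proportion converting to standard vitrectomy with gas, due to inability to seal the FTMH, or detection of peripheral retinal breaks". Repeat vitrectomy with gas is also allowed for holes that fail to close.

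The only planned comparison by surgery received is this: "A secondary analysis will be per protocol comparing those who had gasless vs standard surgery, irrespective of allocation, to investigate the effect of cross-over". It comes directly after the intention-to-treat efficacy sentence and is not stated for safety.

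**The concern.** Two features of the definition could make the arms look more alike on safety than they are.

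- **Denominator.** Someone who is randomised but never has surgery cannot have an intraoperative or postoperative complication. Keeping that person in the denominator lowers the surgical complication rate.
- **Grouping.** Eyes allocated to gasless surgery may leave theatre with gas. If harms are tabulated by allocation only, any gas-related event in those eyes, such as raised intraocular pressure (IOP), appears in the gasless column.

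Collecting preliminary safety data is part of the main clinical aim, and avoiding the harms of gas is the rationale for the new technique. A definition that may understate surgical harm, or may narrow the gas versus gasless contrast, is not cautious when the results are meant to inform a pivotal trial.

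**Working it through.** **Inputs from the protocol article**
- Sample size: 60 in total (30 per arm), at least 28 treated per group, 7% attrition.
- Background: raised IOP in 15.3% to 21.1% of cases with gas.

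**Inputs assumed, because the article gives none**
- *u*, the number per arm never operated on.
- *c*, the number of 30 converted from gasless to gas.
- *b*, the IOP event rate without gas, taken as 5% for illustration.

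**1. The plan's own figure.** 60 × 0.93 = 55.8, about 28 per arm. In reverse, 56 / 0.93 = 60.2. The stated 60 is reproduced to within rounding, and losing 2 of 30 per arm is 6.7%. The article gives no figure for the safety analysis itself.

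**2. Dilution.** Observed rate = true rate × (30 − u) / 30.

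| u of 30 | True 15.3% | True 20% | True 21.1% | Relative loss |
|---|---|---|---|---|
| 0 | 15.3% | 20.0% | 21.1% | 0% |
| 1 | 14.8% | 19.3% | 20.4% | 3.3% |
| 2 | 14.3% | 18.7% | 19.7% | 6.7% |

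The last row puts all of the 7% attrition before surgery, so it is the upper bound under the plan's own assumption. With equal *u* in both arms, the absolute difference shrinks by the same proportion and the ratio of the rates is unchanged. With zero events, the exact 95% upper limit is 11.6% for n = 30 and 12.3% for n = 28.

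**3. Conversion, if harms are grouped by allocation.** Assume that all are operated on and that the control arm all receives gas, with event rate *g*.

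Apparent gasless rate = ((30 − c) × b + c × g) / 30.

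Apparent difference = g − apparent gasless rate = (g − b) × (1 − c/30).

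The difference therefore shrinks by the share converted, whatever *g* and *b* are. With g = 21.1% and b = 5%:

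| c of 30 | Apparent gasless rate | Apparent difference | Shrinkage |
|---|---|---|---|
| 0 | 5.0% | 16.1 points | 0% |
| 3 | 6.6% | 14.5 points | 10% |
| 6 | 8.2% | 12.9 points | 20% |

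For c = 5, the net addition to the gasless arm is 5/30 × (15.3 − 5) = 1.7 points to 5/30 × (21.1 − 5) = 2.7 points.

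**4. Scale of the noise.** For 6 events in 30, the exact 95% confidence interval is 7.7% to 38.6%.

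**The case against.** The strongest reply has five parts.

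- **Size.** At most 1.3 points on a 20% rate is small beside an interval from 7.7% to 38.6%, and some attrition will fall after surgery, since retention is measured at month 6. This stands. The error is nevertheless systematic and avoidable, and a wide interval does not remove it.
- **Timing.** 42 days is a maximum, and randomisation at baseline, as the Intervention section has it, would leave almost no gap. This stands as far as it goes, but the participant timeline, the assignment section and Table 1 all say screening. The conflict itself needs settling.
- **Grouping.** The article says who is in the safety set, not how they are grouped. A detailed statistical analysis plan is said to exist and is not shown, and grouping is often left to it. This stands: misattribution of gas harms is a possibility, not something the article prescribes. The denominator is different, because the article states that rule outright.
- **Allocation is a legitimate view.** Ending with gas is a risk of attempting gasless surgery, cross-over is reported separately, and adverse events count from consent. This stands, and it is why the by-allocation table should be kept.
- **Surgery received has its own bias.** Conversion follows failure to seal the hole or a retinal break, so a column of completed gasless cases leaves out the difficult ones and can flatter the technique. This stands, and it rules out using that column alone.

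A reader might infer that harm rates will be diluted and that gas harms will be charged to the gasless arm. The documents support neither as a certainty. The first needs participants who are never operated on, and the second needs grouping by allocation together with conversions. Nor should five conversions be read as adding 2.6 to 3.5 points of IOP events (5/30 × 15.3% and 5/30 × 21.1%). Those figures are gross and hold only if the gasless rate is zero.

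**Conclusion.** The point holds in a limited form. The stated safety set does not require surgery, although most of the article places randomisation before it. Surgical complication rates can therefore be diluted by between nothing (all operated on) and about 6.7% in relative terms (2 of 30 per arm, all attrition before surgery).

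Separately, the grouping for harms is not stated, and the comparison by surgery received is attached to efficacy. If harms are grouped by allocation, the contrast in gas-related harms shrinks by the share converted.

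The numbers converted and the 5% gasless rate are assumptions. The IOP range comes from cited sources, and the article exempts elevations below 25.0 mm Hg at the day 1 and week 1–2 visits from adverse event recording. The range therefore illustrates scale and does not predict this trial's counts. Neither effect is large beside the sampling error at 30 per arm. The case for change is that the definition is unsuited to surgical harms and cheap to correct.

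**What to change.** 1. Define the safety set for surgical harms as all participants in whom the index vitrectomy was started.
2. Report harms side by side in two ways: by allocation, and by surgery received with three columns (gasless completed, gasless converted to gas, standard with gas).
3. Flag events that follow repeat surgery with gas, since grouping by index surgery would otherwise leave these gas exposures under gasless.
4. List events between consent and surgery separately, for all randomised participants.
5. Reconcile the Intervention section with the participant timeline, the assignment section and Table 1 on when randomisation takes place.
6. Settle the wording before any comparison of harms between arms, so that the grouping is not chosen after seeing the data. If the analysis plan already does this, align the protocol text with it.

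The cost is wording and extra table columns, with no new data and no more participants. The drawbacks are that the converted column will be small and that the completed-gasless column excludes difficult cases, so it must not be read without the by-allocation table.

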**Methods and analysis:**

This randomised, assessor-masked, surgical, feasibility study aims to recruit 60 participants with FTMH from six English National Health Service sites. Participants will be randomised 1:1 to either standard vitrectomy, gas tamponade and postoperative posturing, or to gasless vitrectomy without posturing. Gasless surgery involves folding a hinged flap of internal limiting membrane over the hole, secured by gravity and a viscoelastic gel. Participants attend postoperatively for examination and imaging. The main feasibility outcomes are recruitment and retention rates, cross-over and participant treatment acceptability. The main clinical outcomes are primary FTMH closure (3 months), best-corrected visual acuity (6 months) and adverse events.

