#### Efficacy outcomes

Refracted ETDRS BCVA at 6 months (mean change in ETDRS letter score from baseline).Surgical success (proportion with FTMH closure within 3 months without further FTMH surgery).Area under the BCVA versus time curve (ETDRS letter score).

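### Macular hole closure is a 3-month outcome in the abstract and outcome list, but the analysis section compares it at 6 months

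*Protocol article*

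**What the plan says.** The protocol article gives a time point for closure in three places.

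- **Abstract, Methods and analysis:** "The main clinical outcomes are primary FTMH closure (3 months), best-corrected visual acuity (6 months) and adverse events". Closure and acuity are deliberately given different time points.
- **Efficacy outcomes:** "Surgical success (proportion with FTMH closure within 3 months without further FTMH surgery". This is the only full definition of the closure outcome.
- **Statistical methods for primary and secondary outcomes:** "primary surgical anatomical closure and mean BCVA (change from baseline, and area under the curve (AUC)) will be compared between groups at 6 months", with the tests given as "Fisher’s exact test and Mann-Whitney, respectively". Fisher's exact test is therefore the closure test.

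Three other places bear on the point.

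- **Table 1 and its footnote** require study-eye OCT at months 1, 3 and 6 in both arms. Day 1 and week 1 scans are required in the gasless arm, but "may be omitted at these two visits for participants in the control arm".
- **Who will be blinded?** says that "a masked grader will assess OCT images sent to an independent reading centre" to determine anatomic closure for the efficacy outcome. It gives no time point.
- **Intervention** counts repeat vitrectomy with gas for a hole that has not closed as a failure, with no time limit.

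**The concern.** Closure is one of the named main clinical outcomes, and the results are meant to show whether a pivotal trial looks worthwhile. Read literally, the sentence that assigns the closure test moves the outcome from 3 to 6 months. Closure at 6 months is not listed as an outcome anywhere, and no sentence says that the 6-month comparison uses 3-month status. Both sets of scans will exist, so two analysts working from this text could report different closure rates and each cite the protocol.

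There is a related looseness in the outcome list. Closure within 3 months can mean status at the month 3 scan, or closure seen on any scan up to then. The abstract points to the first reading, but the outcome list does not say so. The distinction matters here because the two arms do not have the same required scans in the first week.

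**Working it through.** **Sample size.** The article gives 60 in total, at least 28 per group and 7% attrition (Sample size). Required total = 56 / (1 − 0.07) = 60.2. In the other direction, 60 × 0.93 = 55.8, or about 28 per group. The stated 60 is reproduced to rounding and does not depend on when closure is assessed. The article gives no alpha, power or assumed closure rate for the closure comparison, so there is no power figure to check.

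**Where the two time points disagree.** Each possible course of an eye is classified below, taking the 3-month outcome as status at month 3 and applying the repeat-surgery rule from Intervention.

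| Course of the eye | Closure at 3 months | Closure at 6 months |
|---|---|---|
| Closed at month 3 and month 6 | success | success |
| Closed at month 3, reopened and open at month 6 | success | failure |
| Open at month 3, closed without surgery by month 6 | failure | success |
| Open at month 3, then re-operated | failure | failure |
| Open at both visits, no surgery | failure | failure |

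Only the second and third rows differ. A hole open at month 3 and then re-operated is a failure either way.

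**Scans available by month 3 (Table 1 and footnote).** Gasless arm: day 1, week 1, month 1, month 3 = 4. Gas arm: month 1 and month 3 = 2, if both early scans are omitted. The extra scans matter only for an eye graded closed on an earlier scan, open at month 3, and still counted as a success.

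**Size of one reclassified eye.** 1/28 = 3.6 percentage points in that arm (1/30 = 3.3 if all 30 are analysed). The effect on a two-sided Fisher's exact test, using assumed counts with 28 per arm, is:

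| Closed, arm A | Closed, arm B | p |
|---|---|---|
| 28 | 26 | 0.49 |
| 28 | 25 | 0.24 |
| 28 | 24 | 0.11 |
| 28 | 23 | 0.051 |
| 28 | 22 | 0.023 |
| 27 | 21 | 0.051 |
| 27 | 20 | 0.025 |

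One eye can carry the result across 0.05, but only when the difference is already near that boundary. These counts are illustrations and do not come from the article.

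**The case against.** The best defence is that the analysis section does not write a second definition. It names primary closure, which is defined once in the outcome list, and puts three outcomes into one sentence. The 6 months fits acuity and may, for closure, mean only when the comparison is run. That is plausible, and it is why the point is a conflict of time points and not two rival definitions. It does not remove the conflict: as written the phrase governs closure, and nothing elsewhere corrects it. The analysis is also exploratory, in a feasibility trial with no single threshold for progression. That stands, and it limits the severity.

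A reader might infer three stronger things that the article does not support.

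- **That the plan favours the gasless arm.** This needs closure at any visit to count. No section says so, and the abstract points to 3-month status. The unequal early scans are a reason to tighten the wording, not evidence of bias.
- **That closure grading is not properly masked.** The assessment section has the attending investigator measure the hole and "subsequently determine if the hole has closed", but the masking section acknowledges unmasked site reading and assigns the efficacy outcome to the masked reading centre. There is no conflict.
- **That the time point could be chosen after seeing data.** The article says a detailed analysis plan was prepared before recruitment. It is not shown and may settle the matter.

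The published gasless closure rates do not size the problem either. The Background gives 91.7% to 100% for five series and 80% of 10 patients for the fibrin glue series. Neither figure says how many eyes change status between months 3 and 6.

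**Conclusion.** The contradiction is real and is not resolved within the article: closure is a 3-month outcome where it is defined and a 6-month outcome where it is tested. It affects only eyes that reopen after month 3 or close without surgery after month 3. Each such eye is worth 3.6 percentage points in its arm at 28 per arm. The article gives no frequency for either event, so the net effect on the comparison is unknown and could be nil. Sample size is untouched. This is a moderate wording correction to an exploratory analysis of a main clinical outcome. The conclusion rests on reading the analysis sentence as written, and the unseen analysis plan may already state the intended time point.

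**What to change.** 1. In the statistical methods section, split the sentence. Compare closure as the outcome defined under Efficacy outcomes, at 3 months, by Fisher's exact test on the masked reading-centre grade. Keep 6 months for acuity change and area under the curve.
2. Under Efficacy outcomes, state that closure within 3 months means closed on the month 3 OCT with no further macular hole surgery before that scan. The additional day 1 and week 1 scans in the gasless arm then cannot act as extra chances of success.
3. If closure at month 6 is of interest, list it as a separate supportive outcome.
4. Check that the analysis plan uses the same wording.

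The cost is a few sentences. No new visits, scans or participants are needed, because OCT at months 3 and 6 is already required in both arms.
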